**Parasitaemia Blood Sampling Schedule for the first 72 hours**

| Hours             | 0 | 8 | 16 | 24 | 32 | 40 | 48 | 56 | 64 | 72 |
|-------------------|---|---|----|----|----|----|----|----|----|----|
| PCR sample        | 1 | 0 | 0  | 1  | 0  | 0  | 0  | 0  | 0  | 0  |
| No of thick films | 2 | 2 | 2  | 2  | 2  | 2  | 2  | 2  | 2  | 2  |
| No. of thin films | 2 | 0 | 0  | 0  | 0  | 0  | 0  | 0  | 0  | 0  |

**Parasitaemia Blood Sampling Schedule Days 7 to 42**

|                    | Day 7 | Days 14, 21, 28,
35 and 42 | Day of failure | Any
additional
visit |
|--------------------|-------|-------------------------------|----------------|----------------------------|
| PCR Sample         | 1     | 1                             | 1              | 0                          |
| No. of thick films | 2     | 2                             | 2              | 2                          |
| No. of thin films  | 1     | 1                             | 1              | 1                          |

The method of counting parasites will be described in the Study Laboratory Procedures Manual including gametocyte counts.

Local quality control of slides is to be assured by reading of slides by 2 different qualified microscopists, reporting independently, with the arithmetic mean of the 2 counts being recorded in the patient record and CRF. In the case of discrepancy, a third microscopist will review the slides and the Site Principal Investigator will make the final classification to be reported in the CRF.

An external quality control of slide reading will be established by an independent laboratory at Swiss Tropical Institute (STI), Basel, Switzerland. The external quality control will be blinded to treatment assignment. STI will examine all slides in the case of suspected recrudescence plus a proportion of slides from each study site. The procedure for quality control will be described in the Laboratory Procedures Manual.

#### **5.1.1.2. Genotyping studies by PCR**

Genotyping by PCR will be used as an exploratory tool to differentiate re-infection (New infection) from recrudescence or relapse (relapse being parasitemia originating from latent hypnozoites).

Samples will be taken for PCR assessment prior to initial dosing on Day 0 and again prior to Day 1 dosing. PCR samples will also be taken from Day 7 whenever parasitological blood samples are taken, and reserved. The PCR analysis will, however, only be performed in the case of reappearance of parasites as judged by a positive microscopy slide.

A common technical protocol will be used for PCR sampling and analysis. PCR samples will be shipped by courier for centralised assessments at STI, Basel, Switzerland for reporting of PCR data conducted for patients classified as treatment failure. Instructions for sampling and storing filter paper for molecular marker studies will be provided in a Laboratory Procedures Manual.

### **5.1.2. Clinical efficacy assessments**

#### **5.1.2.1. Body temperature**

Body temperature will be measured at screening on Day 0 (Pre-Dose) and every 8 hours over at least 72 hours following first study drug administration or when fever has normalised ( $<37.5^{\circ}\text{C}$  axillary/tympanic or  $<38^{\circ}\text{C}$  oral/rectal): 2 normal readings taken between 8 and 24 hours apart. Temperature will be measured at every visit thereafter and as clinically indicated.

Temperature methodology shall be according to local practice. For each individual patient, the same means of temperature measure (axillary, oral, tympanic, rectal) should be used throughout the entire study period. Patients who have had a documented reported history of fever ( $\geq 37.5^{\circ}\text{C}$  axillary/tympanic or  $\geq 38.0^{\circ}\text{C}$  oral/rectal) prior to screening should be monitored closely for fever peaks.

Patients entered in the study on the basis of history of fever and who do not subsequently have at least one body temperature measurement indicating presence of fever will not be included in the analysis of fever clearance time.

Quality of temperature-taking technique and thermometers should be checked and calibrated prior to study commencement and at regular intervals during study.

**5.1.2.2. Clinical signs and symptoms of malaria**

Clinical signs and symptoms of malaria will be assessed during the treatment period, plus on any other occasion where the patient presents to the site, when clinically indicated. The following signs and symptoms will be specifically assessed: rigors/chills, sweating, headache, nausea, vomiting, cough, loss of appetite/anorexia, fatigue (asthenia/lethargy/malaise), myalgia (back and limbs), jaundice (hyperbilirubinemia), hepatomegaly and splenomegaly.

If any sign or symptom of acute malaria represents a clinically significant worsening compared to the patient's baseline condition, which are considered to be more severe than normal daily fluctuation of the disease process, then this should be recorded as an adverse event.

**5.1.3. Drug levels at time of treatment failure**

At time of suspected treatment failure, prior to administration of rescue treatment, a 1 mL of whole blood sample will be drawn for assay of pyronaridine and/or chloroquine (and metabolites) levels.

For full details on sample handling procedures, see Attachment 6.

The actual times of sampling will be recorded in the CRF.

**5.1.4. Population pharmacokinetics**

At selected clinical study sites, as determined by the Sponsor, the Investigator is required to collect samples as follows:

- ◆ Sampling for Pyronaridine Population Pharmacokinetics: 2 blood samples from each patient at two different timepoints. One sample will be drawn between Day 0 (post dose) and Day 3, and a second between Day 4 and Day 42.
- ◆ Sampling for Artesunate Population Pharmacokinetics: 2 plasma samples from each patient at two different timepoints. One sample will be drawn on Day 0 (post-dose) or Day 2, and a second one on Day 3.

A list of timepoints will be generated corresponding to each patient number and provided to the Principal Investigator. Actual time must be recorded

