| Concomitant Treatment      | 
The administration of paracetamol/acetaminophen (<math>\leq 1</math> g) on Day 0, 1 and 2 is allowed if the patient's condition warrants it and should be recorded in the appropriate section of the CRF.
 
Rescue treatment: Treatment failures will be treated with best antimalarial therapy available in the country where the study is conducted.
 
If during follow-up, infections other than malaria require the administration of drugs with antimalarial activity (such as co-trimoxazole, tetracycline or doxycycline), the patient will be considered a protocol violator, with the exception of patients given tetracycline as eye ointment.
 
All concomitant medications taken by the patient during the study, from the date of signature of the informed consent will be recorded in the appropriate section of the CRF.
                                                                                                                                                            |
| Study Drugs Administration | 
Study drug will be administered orally once a day for three consecutive days, i.e. on Days 0, 1 and 2, by authorized member of the investigation team.
 
Depending on their body weight, patients will receive a total of between 2 to a maximum of 8 tablets per day on Days 0 and 1 and a total of between 1.5 to a maximum of 6 tablets per day on Day 2.
                                                                                                                                                                                                                                                                                                                                                                                                                                                                                                                                                                                                                                                  |

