|                                     | 
Additional Assessments:
 
Characterization of pyronaridine and artesunate kinetics will be conducted using a population pharmacokinetic approach.
                                                                                                                                                                                                                                                                                                                                                                                                                                                                                                                                                                                                                                                                                                                                                                                                                                                                                                                                                                                                                                                                                                                                                                                                                                                                                                                                                                                                                                                                                                                                                                                                                                                                                                                                                                                                                                                                                                                                                                                                                                                                                                                                                                                                                                                                                                                                                                                                                                                                                                                                                                                                                                                                                                                                                  |

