Moreover the pharmacokinetic profile of the combination therapy revealed that the artesunate component has a short elimination half-life and the pyronaridine component has an intermediate half-life. Blood pyronaridine and plasma artesunate exhibited approximate linear dose proportionality over the dose range: 6:2 to 15:5 mg/kg (pyronaridine:artesunate respectively) in the single dose study. Absorption was rapid, with a  $T_{max}$  of 1.6 to 4.8 h. for pyronaridine and 0.6 to 0.9 h. for artesunate. The elimination half-life ranged from 6.6 to 9.7 days for pyronaridine, 0.44 to 0.53 h. for artesunate, and 0.9 to 1.5 h. for DHA. Pharmacokinetic analyses show that blood pyronaridine concentrations accumulate with repeated daily doses, whereas plasma artesunate and DHA concentrations do not. Furthermore the food effect study does not suggest any clinically relevant effect of food on the bioavailability of either compound.

The data from the phase I study supported the transition for the combination product into adult patients with acute uncomplicated malaria. The pharmacokinetic profile after single and multiple doses regimens supports once-daily dosing.

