#### **4.5. Drug Administration**

Study drug will be administered to patients by a qualified member of the study site who has been designated by the Investigator. All parties will be blind to treatment assignment and will not be informed of treatment allocation unless the blind needs

to be broken for a medical emergency. Sealed envelopes with treatment allocation will be available at each site to be opened only in case of emergencies. Patient's weight at screening should be used to calculate the number of tablets to be administered.

Study drug will be given to each patient with up to 240 ml (full glass) water. All tablets must be swallowed. Patients will take the medication in an upright position (seated or standing). The patient may be given food prior to drug administration. Initial drug administration day is designated Day 0. A dispensing record detailing the number of tablets administered for each patient, as well as the date and time, will be maintained. Exact time of dose administration will be recorded in the CRF. Dosing on the two subsequent days will occur no less than 10 hours after the previous dosing. Exact time of daily dose administration will be recorded in the CRF.

In the case of a patient vomiting the first dose (Day 0) within 0 to 30 minutes of study drug administration, a repeat full dose will be given. If patient vomits the study drug on either the second (Day 1) or third day (Day 2) of dosing or if the patient vomits a re-administered dose on Day 0, they will not be re-dosed and will be withdrawn from the study. A patient who is withdrawn due to vomiting must be given rescue medication.

Unused medication will remain in a locked cabinet in the pharmacy until full accountability has been performed by the Sponsor or its designee and instructions given for their return to Shin Poong.

Patients with normal G-6-PD activity (as at screening) and who complete the study up to Day 28 will be given a 14-day course of primaquine (15 mg/day) in an open-label manner starting on Day 28, after all required assessments have been completed. For women of childbearing potential, a negative pregnancy test should be demonstrated before starting primaquine treatment. Primaquine treatment should not be administered to pregnant women.

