a) For patients with normal G-6-PD activity, oral primaquine treatment (once daily for 14 days) will be started on Day 28, after all assessments have been performed (including confirmation of negative pregnancy test for women of childbearing potential).

b) Every 8 hours over at least 72 hours following the first study drug administration or temperature normalisation for at least two readings 8 and 24 hours apart, then at each visit.

c) If clinically indicated and any day in case of fever.

d) If clinically indicated.

e) Should be performed only if clinically significant abnormalities are observed.

f) Thick blood films will be examined every 8 hours until at least 72 hours or until a negative smear had been recorded for at least between 8 hours and 24 hours apart, then at each visit.

g) Thin blood smear will also be taken from Day 7 whenever parasitological blood samples are taken, and reserved in the event of recrudescence, to confirm *Plasmodium* species.

h) A blood sample to measure pyronaridine levels must be taken in case of treatment failure. Furthermore, for pyronaridine population PK, 1 sample will be taken between D0 (post-dose) and D3 and another between D4 and D42. For artesunate PK, 1 sample will be taken on D0 (post-dose) or on D2 and a second one on D3.

i) PCR samples will be collected and reserved. Centralized PCR analysis will be performed at baseline and in case of re-appearing parasitaemia.

j) If feasible

k) For females of childbearing potential.

## Attachment 3

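### The second artesunate PK sample falls on Day 3, a no-dose day nominally 24 h after the last dose, so on the protocol's own half-lives it is very likely below quantification and adds little

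*Protocol*

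**What the plan says.** The Synopsis (Additional Assessments) sets the aim: "Characterization of pyronaridine and artesunate kinetics will be conducted using a population pharmacokinetic approach". Section 5.1.4 asks, at sites chosen by the sponsor, for "2 plasma samples from each patient at two different timepoints", timed as follows: "One sample will be drawn on Day 0 (post-dose) or Day 2, and a second one on Day 3". The population PK row in Section 6 gives the same days, and so does footnote h of the Attachment 2 study plan: "For artesunate PK, 1 sample will be taken on D0 (post-dose) or on D2 and a second one on D3".

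On dosing, the Synopsis states: "Study drug will be administered orally once a day for three consecutive days, i.e. on Days 0, 1 and 2". Section 4.5 fixes the numbering: "Initial drug administration day is designated Day 0". It also sets a minimum spacing between doses: "Dosing on the two subsequent days will occur no less than 10 hours after the previous dosing". No clock time is fixed for the Day 3 PK draw. Individual timepoints are to come from a list issued for each patient number.

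The phase I summary in the Introduction gives elimination half-lives of "0.44 to 0.53 h. for artesunate, and 0.9 to 1.5 h. for DHA". It reports that pyronaridine builds up over repeated daily doses, whereas artesunate and DHA do not.

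**The concern.** Day 3 is a no-dose day. Without accumulation, only the Day 2 dose can contribute to a Day 3 sample, and both the parent drug and its active metabolite are eliminated within hours. The schedule therefore places one of the two artesunate samples where almost nothing is left to measure. The pyronaridine schedule does not share the problem, because that half-life is reported in days.

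At stake is how much the artesunate population analysis can learn. With two informative samples per patient, differences between patients can be distinguished from noise within a patient. With about one, they hardly can. Patients, children among them, would also give a tube of blood for little return. An analysis plan cannot recover this, because the sampling day is set in the protocol.

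**Working it through.** **Inputs**
- Last dose on Day 2; second artesunate sample on Day 3 (Synopsis; Sections 4.5, 5.1.4 and 6; Attachment 2). Nominal interval t = 24 h.
- Half-life h: artesunate 0.44 to 0.53 h, DHA 0.9 to 1.5 h (phase I summary; healthy subjects).
- The non-clinical summary gives 25 to 60 minutes after oral administration, used as a cross-check.
- Assay limit and peak concentration: not in the documents. Assumed ranges are 0.1 to 5 ng/mL and 500 to 10,000 ng/mL.

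**The plan's own figure.** Table 2 lists four 1 ml drug-level samples. Two for pyronaridine plus two for artesunate gives 2 + 2 = 4, which agrees. The Day 3 tube is 1 of the 2 artesunate samples.

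**Formulas.** Elapsed half-lives = t / h. Fraction of peak remaining = 2^(-t/h), ignoring the short absorption phase.

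**At the nominal 24 h**
- DHA: 24/1.5 = 16.0 to 24/0.9 = 26.7 half-lives; fraction 1.5 × 10^-5 down to 9.4 × 10^-9.
- Artesunate: 24/0.53 = 45.3 to 24/0.44 = 54.5 half-lives; fraction 2.3 × 10^-14 down to 3.8 × 10^-17.
- Cross-check with 25 to 60 minutes: 24 to 57.6 half-lives; fraction at most 6.0 × 10^-8.
- For even 1% to remain at 24 h, the half-life would have to be 24 / log2(100) = 3.6 h, more than twice the longest figure reported.

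**Against the assumed assay limits, slowest DHA half-life, 24 h**
- Peaks of 500 to 10,000 ng/mL leave 500 × 2^-16 = 0.008 to 10,000 × 2^-16 = 0.15 ng/mL.
- To read at the limit, the peak would have to be about 6,550 ng/mL (limit 0.1), 65,500 (limit 1) or 328,000 (limit 5). Only the corner with a very sensitive assay and a high peak gives a measurable value.

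**Sensitivity to the draw time.** The interval from the Day 2 dose to the Day 3 draw is not fixed, so a late dose followed by an early draw is possible.

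| Interval | DHA half-lives | DHA left, at most | Artesunate left, at most |
|---|---|---|---|
| 10 h | 6.7 to 11.1 | 0.98% | 2.1 × 10^-6 |
| 12 h | 8.0 to 13.3 | 0.39% | 1.5 × 10^-7 |
| 16 h | 10.7 to 17.8 | 0.06% | 8.2 × 10^-10 |
| 24 h | 16.0 to 26.7 | 0.0015% | 2.3 × 10^-14 |

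At 12 h with the slowest half-life, the assumed peaks leave 500 × 0.0039 = 2 to 10,000 × 0.0039 = 39 ng/mL of DHA, which may be measurable. With the fastest half-life the range is about 0.05 to 1 ng/mL. For parent artesunate, even at 10 h and taking a peak of 10,000 ng/mL, 10,000 × 2.1 × 10^-6 = 0.02 ng/mL remains, below the lowest assumed limit.

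**The case against.** Several objections have weight and limit how far the point can be taken.

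- **Timing.** A reader might infer that 16 DHA half-lives is a floor. It is not: it belongs to the nominal 24 h. A draw 10 h after a late Day 2 dose would come after about 6.7, and DHA might then be measurable in a patient who eliminates it slowly. The half-lives also come from healthy subjects, not patients with vivax malaria.
- **Information.** A reader might infer that the Day 3 samples carry none at all. That depends on an assay limit the documents do not state, and a result below the limit still gives a weak upper bound.
- **Estimability.** A reader might infer that one informative sample per patient makes clearance and volume inseparable. The documents do not support this. The approach is a population one with patient-specific timepoints, so first samples spread over post-dose times can be pooled to inform typical apparent clearance and volume. What suffers is the separation of between-patient variability from residual error.
- **Day 2 option.** It lacks the post-dose label that Day 0 carries, and a reader might infer that troughs are planned. Day 0 also includes screening and pre-dose procedures, which may explain the label there. This calls for clarification and does not show a second fault.
- **Importance.** Population PK is an additional assessment at selected sites and is not among the listed endpoints.

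The objection that the patient-specific list will repair the schedule fails. The protocol text confines every second artesunate sample to Day 3, so the list can choose only the hour.

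**Conclusion.** The schedule and the protocol's own half-lives do not fit together. At the nominal 24 h, at most 1.5 × 10^-5 of peak DHA and about 2 × 10^-14 of peak artesunate remain. The second of the two artesunate samples is therefore very likely below quantification and adds little. The main exception is an early Day 3 draw after a late Day 2 dose, with slow elimination and DHA among the analytes. The protocol names artesunate concentration and does not say that DHA will be assayed; if only the parent is measured, the case is stronger.

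This rests on the phase I half-lives carrying over to patients and on an assay limit of ordinary size relative to peak, which is an assumption. The consequence is about one informative artesunate sample per patient on the combination, and poor separation of between-patient variability from residual error. The effect stops there: the efficacy and safety endpoints are unaffected. It is worth correcting because the change is small and the loss cannot be made good once sampling has ended.

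**What to change.** Move the second artesunate sample to a post-dose time on a dosing day, or state why Day 3 was chosen. Set the windows from the phase I half-lives, the analyte or analytes assayed and the assay limit, and spread them across patients through the existing time list. The analyte matters: by 6 h after a dose, parent artesunate is already at 2^(-6/0.53) = 0.04% of peak or less, while DHA is between 2^(-6/0.9) = 1% and 2^(-6/1.5) = 6%.

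State that the Day 2 option is post-dose. Align Section 5.1.4, the population PK row of Section 6, footnote h of Attachment 2 and the Attachment 2 grid. As the grid reads here, it marks drug concentrations from Day 1 onward and not on Day 0, whereas the footnote includes Day 0.

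The cost is a small protocol amendment, which under Section 7.5 must be notified to or approved by each ethics committee before use. The number of samples and the blood volume in Table 2 do not change, and patients are already kept at the facility on the dosing days.
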